## **9. DISEASE EVALUATION AND METHODS**

The response to immunotherapy may differ from the typical responses observed with cytotoxic chemotherapy including the following (Wolchok et al 2009, Nishino et al 2013):

- Response to immunotherapy may be delayed
- Response to immunotherapy may occur after PD by conventional criteria
- The appearance of new lesions may not represent PD with immunotherapy
- SD while on immunotherapy may be durable and represent clinical benefit.

Based on the above-described unique response to immunotherapy and based on guidelines from regulatory agencies, e.g., European Medicines Agency's "Guideline on the evaluation of anti-cancer medicinal products in man" (EMA/CHMP/205/95/Rev.4) for immune modulating anti-cancer compounds, the study may wish to implement the following in addition to standard RECIST 1.1 criteria:

- RECIST will be modified so that PD must be confirmed at the next scheduled visit, preferably, and no earlier than 4 weeks after the initial assessment of PD in the absence of clinically significant deterioration. Treatment with durvalumab + tremelimumab would continue between the initial assessment of progression and confirmation for progression.
- In addition, subjects may continue to receive durvalumab + tremelimumab beyond confirmed PD in the absence of clinically significant deterioration and if investigators consider that subjects continue to receive benefit from treatment.

Modification of RECIST as described may discourage the early discontinuation of durvalumab + tremelimumab and provide a more complete evaluation of its anti-tumor activity than would be seen with conventional response criteria. Nonetheless, the efficacy analysis will be conducted by programmatically deriving each efficacy endpoint based on RECIST 1.1 criteria.

Of note, clinically significant deterioration is considered to be a rapid tumor progression that necessitates treatment with anti-cancer therapy other than durvalumab + tremelimumab or with symptomatic progression that requires urgent medical intervention (e.g., central nervous system metastasis, respiratory failure due to tumor compression, spinal cord compression).>>

## **9.1. RECIST 1.1 criteria**

Patients will undergo regular tumor assessments until documented disease progression as described by RECIST 1.1 criteria. CT scan performed at the following time point: screening (baseline); Cycle 6; Cycle 12 and Cycle 18

Response criteria are essentially based on a set of measurable lesions identified at baseline as target lesions, and followed until disease progression.

The following paragraphs are a quick reference to the RECIST criteria.

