**STEP 2: Efficacy Assessments**

- 1) RECIST 1.1 criteria evaluated in TDM imaging every 3 months,
- 2) irRC (Immune Related Response Criteria) methods,
- 3) Progression free survival (PFS, RECIST 1.1 criteria),
- 4) Overall survival (OS).

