## 9.2. Modified irRC methods

- Overall irCR: Complete disappearance of all lesions (whether measurable or not) and no new lesions. All measurable lymph nodes also must have a reduction in short axis to 10 mm or less.
- Overall irPR: Sum of the longest diameters of target and new measurable lesions decreases  $\geq 30\%$ . (compared to baseline)
- Overall irSD: Sum of the longest diameters of target and new measurable lesions neither irCR, irPR, (compared to baseline) or irPD (compared to nadir).
- Overall irPD: Sum of the longest diameters of target and new measurable lesions increases  $\geq 20\%$  (compared to nadir), confirmed by a repeat, consecutive observations at least 4 weeks (normally it should be done at 6 weeks) from the date first documented

|                               | RECIST 1.1                                                                                                                                                                     | Modified IrRC                                                                                                                                                                       |
|-------------------------------|--------------------------------------------------------------------------------------------------------------------------------------------------------------------------------|-------------------------------------------------------------------------------------------------------------------------------------------------------------------------------------|
| Target /
Index Lesions     | Up to 5 total (2/organ)
unidimensional                                                                                                                                      | Up to 5 total (2/organ), unidimensional                                                                                                                                             |
| New lesions                   | Always represent PD                                                                                                                                                            | Incorporated into SOLD if $\geq 5 \times 5$ mm
(non-nodal) or $\geq 10$ mm (nodal)                                                                                               |

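### The protocol gives conflicting end points for tumour assessment: section 9.1 stops scans at first RECIST 1.1 progression, while the irPD definition and several other sections rely on confirmed progression

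*Protocol*

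**What the plan says.** The synopsis lists "irRC (Immune Related Response Criteria) methods" as the second Step 2 efficacy assessment, beside RECIST 1.1, PFS and OS.

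On how long patients are scanned, section 9.1 says: "Patients will undergo regular tumor assessments until documented disease progression as described by RECIST 1.1 criteria". It continues: "CT scan performed at the following time point: screening (baseline); Cycle 6; Cycle 12 and Cycle 18".

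On confirmation, section 9 opens with "the study may wish to implement the following in addition to standard RECIST 1.1 criteria" and then says: "RECIST will be modified so that PD must be confirmed at the next scheduled visit, preferably, and no earlier than 4 weeks after" the first assessment of PD, unless there is clinically significant deterioration. The same section gives the reasons: response to immunotherapy may be delayed, may follow conventional PD, and new lesions need not mean progression. Section 9.2 makes confirmation part of the definition of irPD, which must be "confirmed by a repeat, consecutive observations at least 4 weeks (normally it should be done at 6 weeks) from the date first documented".

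Three further places presuppose confirmed PD: item 10 of section 4.3 (stopping study drug), section 9.4 (continued tumour assessments in patients withdrawn for other reasons) and section 10.2.1 (where tumour assessments end for patients who stop treatment for reasons other than progression).

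Section 9 also states that every efficacy endpoint will be derived by RECIST 1.1.

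**The concern.** One protocol holds two stopping points for tumour assessment, first PD and confirmed PD. They are incompatible for any patient whose first progression is seen on a scan.

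At stake is the irRC assessment. The immune-related criteria were added because section 9 expects some patients to respond, or to prove stable, after progression by conventional criteria. Those patients can be recognised only by a scan made after the first PD. If some sites follow 9.1 and others follow section 9 or the visit schedule, post-progression imaging will exist for some patients and not for others, depending on which section the site read. Scans not made cannot be recovered at analysis.

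**Working it through.** This is a comparison of text, with two short calculations.

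**1. What 9.1 means by progression.** The comparison table in 9.2 has a RECIST 1.1 column and a modified irRC column. The RECIST column asks for confirmation of CR and PR but not of PD. The irRC column asks for confirmation of PD at 4 weeks or more. Documented RECIST progression in 9.1 is therefore the first PD.

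**2. What follows if 9.1 governs.** Take a patient with RECIST PD at Cycle 6. No later scan is made, so confirmed irPD is unobtainable and later irSD, irPR or irCR cannot be seen.

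**3. What can still be scored on that one scan.** Under RECIST, new lesions "Always represent PD". Under modified irRC, measurable new lesions are added to the sum of diameters, and non-target lesions count only towards irCR. A patient with RECIST PD through a new or non-target lesion, whose total sum has risen by less than 20% from nadir (and has not fallen by 30% from baseline), is irSD on that scan. The irSD definition asks for no confirmation. A rise of 20% or more needs the repeat scan.

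**4. Whether other sections settle the conflict.**
- Section 9 asks for confirmation, but under permissive wording. The firm requirement is the irPD definition in 9.2.
- Sections 9.4 and 10.2.1 mainly concern patients off treatment for reasons other than PD. Section 9.4 refers the reader to Appendix 3, which contains durvalumab dose volume calculations.
- The imaging footnote to the schedule sets CT every 3 months at fixed times and states no stop at first PD. It requires confirmatory scans for CR and PR, and is silent on PD.
- Sections 9.1 and 8.1.2 list on-treatment CT at Cycles 6, 12 and 18 only. The schedule marks CT at V6, V12, V18, V24, V30, V36, V42 and V48.

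**5. Timing.** With 2-week cycles, week = (cycle − 1) × 2. Cycle 6 is week 10, Cycle 12 is week 22 and Cycle 18 is week 34, so the gap is 12 weeks. The next scheduled CT satisfies the 4-week minimum in sections 9 and 9.2, but not the usual 6 weeks in 9.2.

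**6. Upper bound on numbers.** Section 11.4 takes median PFS of 3 months as uninteresting and 6 months as expected. With exponential survival:
- Progression-free at 3 months = 0.5^(3/3) = 0.50 and 0.5^(3/6) = 0.707, which reproduces the plan's 50% and 70.7%.
- Events by month 3 among the 43 evaluable patients = 43 × (1 − 0.707) = 12.6, and 43 × (1 − 0.50) = 21.5. That is 13 to 22.
- Events by month 6 = 43 × (1 − 0.5^(6/6)) = 21.5, and 43 × (1 − 0.5^(6/3)) = 32.3.

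These counts include deaths, the symptomatic progression that 9.3 allows, and the patients in step 3 who can be scored. The radiological share is not stated.

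**7. The primary decision.** Section 11.3.2 counts RECIST CR, PR or SD at 3 months, with 26 or more of 43 required. Section 11.3.4 requires 9 or more of the first 16 to continue. Neither count uses irRC or a post-progression scan. The exact properties of the rule (type I error 0.093 at 50%, power 0.901 at 70.7%) do not change.

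**The case against.** The strongest case against is that 9.1 is only the RECIST subsection and does not forbid later scans. Section 9 provides a confirming assessment. The schedule continues CT every 3 months to V48. Section 8.1.3 includes CT at end of treatment unless one was done in the previous 28 days. Section 5.2.2 requires a new baseline scan and further scans for patients retreated after PD. The objectives name PFS, response and OS without irRC, and the protocol describes no irRC analysis.

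Much of this stands. A reader might infer that irRC cannot be scored in exactly the patients where it differs from RECIST, or that irRC results would come only from patients in whom the criteria agree. The documents do not support either. The first holds only if 9.1 overrides section 9, 9.4, 10.2.1 and the schedule. The second is contradicted by the irSD classification in step 3 of the working. For the same reason, it does not follow that the confirmed-PD criterion in 4.3 can never be met. Nor are 13 to 22 of 43 an estimate of patients lost.

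The objection does not remove the conflict. No section states that it overrides 9.1, and an assessment listed for Step 2 needs imaging that 9.1 ends.

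**Conclusion.** The point holds as a contradiction to be reconciled, confined to the irRC assessment. If 9.1 is followed literally, confirmed irPD and any response after first RECIST PD are lost, while RECIST progressors by new or non-target lesions with a rise below 20% in the sum of diameters can still be called irSD at that scan. If the other sections are followed, the next scheduled scan allows irPD to be scored.

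The number affected cannot be derived from the documents. The month-3 figure of 13 to 22 of 43 is an upper bound at that time. It assumes the plan's two progression-free rates and counts every PFS event as if it were a radiological progression needing a repeat scan. Later progressors would add to it.

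PFS, RECIST response and the Simon decision are not affected, so this is worth correcting but does not threaten the main conclusion.

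**What to change.** Reconcile sections 9, 9.1, 9.2, 9.4 and 10.2.1 around one end point for tumour assessment:

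- State in 9.1 that assessments continue after first RECIST 1.1 PD until PD or irPD is confirmed or refuted, or until new anticancer therapy or death.
- Name the next scheduled CT, about 12 weeks later, as the confirming scan, and bring the 6-week wording in 9.2 into line with the schedule.
- State that RECIST 1.1 PFS remains dated at first PD and that the later scan serves irRC.
- Replace the permissive opening in section 9 with a definite statement, align the CT lists in 9.1 and 8.1.2 with the schedule, and correct the Appendix 3 reference in 9.4.

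The cost is wording. Using the next scheduled CT adds no procedure beyond the current schedule, whereas a dedicated 6-week scan would add an unscheduled CT. The price of the 12-week interval is that some patients may start another therapy before the confirming scan. They should be reported as unconfirmed. Where the sections differ on stopping or continuing treatment at progression, they must also be reconciled; no view is offered here on which rule should apply.

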- i CT (preferred) or MRI scans, preferably with IV contrast, are collected during screening (for baseline) and as close to and prior to initiation of study treatment. Response according to RECIST 1.1 criteria (CR, PR) requires a confirmatory scan preferably at the next regularly scheduled imaging visit and no earlier than 4 weeks after the prior assessment of CR, PR, or SD. CT scan evaluation should be performed every 3 months at fixed time.
- j For AEs/SAEs reported during prescreening additional information such as medical history and concomitant medications may be needed.
- k Blood sampling must be done at visit 12. If patient stops the study before visit 12, blood samples must be drawn at end of study visit (EOT). If blood sampling is performed at visit 12, no need to perform blood sampling at EOT.
- l A new biopsy is required only if no sufficient archiving material is available
- m Biopsy use for principal study will be used for ancillary study (archiving material or fresh biopsy). If the cure is postponed, the biopsy must be postponed as well. Biopsies should always match C5, C12.
- n Blood sample performed only if patient signed the genetic informed consent form
- o If the cure is postponed, the blood samples for ancillary study must be postponed as well. Biological samples have to be collected at cycle 1-2-5 and 12 (or EOT).

| TABLE OF CONTENTS                                                                        | PAGE |
|-------------------------------------------------------------------------------------------------|-------------|
| DESIGN OF THE STUDY .....                                                                       | 2           |
| PROTOCOL SYNOPSIS .....                                                                         | 3           |
| TABLE OF CONTENTS.....                                                                          | 17          |
| ABBREVIATIONS AND DEFINITION OF TERMS.....                                                      | 22          |
| 1. INTRODUCTION .....                                                                    | 26   |
| 1.1 Disease Background .....                                                             | 27   |
| 1.1.1 Immunotherapies.....                                                                      | 28          |
| 1.1.2 Durvalumab .....                                                                          | 28          |

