### **5.3.2 Product preparation, Doses and treatment regimens administration**

Subjects will be administered with FOLFOX in line with normal clinical practice, with a dose and schedule of Oxaliplatin, 85 mg/m^2 administered as intravenous infusion over 2 hours in 250 ml dextrose 5% or sterile water for injection concurrently (via a Y-connector) with LV, 400 mg/m^2 (400 mg/m^2 for form dl or 200 mg/m^2 for form l) administered as intravenous infusion over 2 hours, in 250 ml dextrose 5%, or sterile water for injection followed by 5-FU, 400 mg/m^2 administered as a bolus injection (intravenous push administered manually in approximately 2 minutes), followed by 5-FU, 2400 mg/m^2 administered as a intravenous infusion over 46 hours. Oxaliplatin should always be administered before fluoropyrimidines.

Dose of oxaliplatin, 5-FU and LV will be administered on the basis of milligrams of each drug per square meter of body surface area (BSA) as measured at baseline (mg/m^2). The dose of oxaliplatin administered should be as close as possible to the calculated dose and will be limited to a maximum BSA of 2.0 m^2. Though the weight of the patient may change throughout the study, BSA will be assumed to stay close to that measured at baseline, i.e. no dose adjustments for changes in body weight will be done unless weight loss alone is considered to be an adverse event of grade 2 or more. Cycle length is 2 weeks comprising approximately 48 hours of infusion and 12 days of rest. It is expected that subjects will receive between 1 and 12 cycles of FOLFOX (6 months).

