### **8.1.2 Treatment Phase**

Procedures to be conducted during the treatment phase of the study are presented in the Schedule of Assessments table 1. Screening procedures performed within J28 to J-1 of Cycle 1 Day 1.

- Complete physical exam
- ECOG Performance Status
- Weight
- Vitals signs to be performed before infusion and should also be repeated 30mn after tremelimumab and durvalumab infusion
- 12-lead ECG if clinically indicated
- Review of prior/concomitant medications
- Imaging by CT scan at Cycle 6, 12 and 18
- Clinical laboratory tests scheduled as described in the schedule of assessment:
  - Hematology (see Table 3)
  - Clinical chemistry (see Table 4)
  - TSH
  - Coagulation (PT, PTT, INR)
  - Creatinine Clearance
  - Serum pregnancy test (for women of childbearing potential only) and if clinically indicated
  - Hepatitis serologies
  - Urinalysis (see Table 5)

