### **11.3.2. Efficacy Analyses set**

Efficacy analyses will be performed in modified intent-to-treat population (ITT) population ie, all patients following the major inclusion criteria and with a 3 months evaluation. Analyses will be repeated in the intent to treat principle i.e including all enrolled patients whatever eligibility criteria and treatment received patients and in the per protocol population (patients who had received all the planned doses).

The primary objective will be evaluated at 3 months among MSS patients only. According to the Simon's design, at 3 months, on the first evaluable 43 patients (mITT population): if 26 or more patients respond to treatment the treatment will be considered of interest for evaluation in a phase III trial. Response rates will be evaluated using RECIST criteria. Response will be considered for patient with Complet response (CR), partial response (PR) and stable disease (SD). Overall survival and progression free survival (OS and PFS) will be estimated using Kaplan Meier method. Median survivals will be reported with 95% confidence intervals (CI).

Median follow-up will be estimated using the reverse Kaplan Meier method.

Analysis of survival and response among MSI patients will be performed in an exploratory manner, taken into account the small sample size in this population. All statistical analysis will be performed with Stata 11 or SAS 9.3.

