#### **11.4. Determination of sample size**

**Step 1:** Nine patients will be included in the **safety** analyses. If the same grade 3-4 adverse event is reported for more than 1 patient over 3, the trial could prematurely stop after reunion of the independent committee. Patients from the safety population will be included in the efficacy set.

**Step 2:** The **efficacy** will be determined using a Simon 2 steps phase II design.

The hypotheses are the following:

The primary objective will be evaluated among MSS patients

A PFS of 3 months is not considered of interest. A PFS of 6 months is expected. This is equivalent to assume that a PFS of 50% at 3 months is insufficient and a PFS of 70.7% is expected. With  $\alpha=10\%$ ,  $\beta=10\%$  (90% power), 20% of non-evaluable patients, 52 patients with MSS disease are needed including patients of the safety population (9 patients)

The prevalence of MSS disease is around 90%-95%, thus 5 additional patients will be included

Overall the study will include 57 patients.

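### The protocol ties the primary CT to Cycle 6 in some places and to a fixed 3 months in others, but the decision rule keeps its 10% alpha only if status is read about 3 months from enrolment

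*Protocol*

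**What the plan says.** Two sets of statements fix the time of the first on-treatment CT.

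**By cycle.** Section 9.1: "CT scan performed at the following time point: screening (baseline); Cycle 6; Cycle 12 and Cycle 18". Section 8.1.2: "Imaging by CT scan at Cycle 6, 12 and 18". Figure 1a marks the scan under V6. Section 5.3.2 gives the cycle length: "Cycle length is 2 weeks comprising approximately 48 hours of infusion and 12 days of rest".

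**By calendar.** Footnote i to the assessment schedule: "CT scan evaluation should be performed every 3 months at fixed time". The synopsis, under Step 2 efficacy assessments: "RECIST 1.1 criteria evaluated in TDM imaging every 3 months". Section 11.3.2: "The primary objective will be evaluated at 3 months among MSS patients only". Section 9.3 collects PFS data at months 3 and 6 and counts PFS from enrolment.

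**The hypotheses are set at 3 months.** Section 11.4: "A PFS of 3 months is not considered of interest. A PFS of 6 months is expected", and then "This is equivalent to assume that a PFS of 50% at 3 months is insufficient and a PFS of 70.7% is expected". Sections 11.3.4 and 11.3.2 give the rule: continue with at least 9 successes among 16 evaluable patients, and call the treatment of interest with at least 26 among 43. A success is complete response, partial response or stable disease.

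**The concern.** A success here is in effect a patient who has not progressed when scanned, so the success rate depends directly on when the scan is done. An earlier scan raises it for any regimen, including one that section 11.4 calls of no interest.

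A cycle anchor and a fixed calendar anchor disagree even when no cycle is delayed. With delays they drift further apart, and differently for each patient. If sites follow sections 8.1.2 and 9.1, status may be read before the time to which the 50% null and both cut-offs belong. The next scheduled CT is at V12, week 22 after Day 1, so no later planned scan would close the gap to month 3.

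This is a single-arm trial, and the threshold in section 11.3.2 decides whether a phase III trial is considered. Reading too early weakens both the stage 1 futility stop and the final test.

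**Working it through.** **1. When Cycle 6 falls.** With 2-week cycles, visit n is at week 2(n − 1). Two other statements confirm the count: section 5.2.1 has eight 2-weekly durvalumab doses and continuation from week 16 (V9: 2 × 8 = 16), and the heading of the schedule gives 26 doses with the last at week 50 (2 × 25 = 50). V6 is therefore at week 2 × 5 = 10 after Day 1. The end of Cycle 6 is week 12.

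**2. The protocol's own figures.** The value 70.7% is 0.5^(3/6), and 50% is 0.5^(3/3). The plan thus assumes exponential PFS with medians of 6 and 3 months. For a success probability p, the exact probability of declaring success is

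P(p) = Σ over x = 9 to 16 of Pr[Bin(16, p) = x] × Pr[Bin(27, p) ≥ 26 − x].

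At p = 0.50 this is 0.093. At p = 0.707 it is 0.901. Both agree with the stated alpha of 10% and power of 90%. A search over two-stage designs returns the same numbers (8/16, 25/43) as the optimal Simon design, so the rule itself is correct at 3 months.

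**3. The same rule read at other times.** With t in months (days/30.44) from the PFS origin, the progression-free proportion is 0.5^(t/3) under the null and 0.5^(t/6) under the alternative. For week 10: t = 70/30.44 = 2.30, 0.5^(2.30/3) = 0.588 and 0.5^(2.30/6) = 0.767.

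| Weeks from PFS origin | t (months) | Null rate | Alternative rate | P(success), null | P(stop at stage 1), null | Power |
|---|---|---|---|---|---|---|
| 10 | 2.30 | 0.588 | 0.767 | 0.417 | 0.319 | 0.979 |
| 11 | 2.53 | 0.557 | 0.747 | 0.276 | 0.413 | 0.962 |
| 12 | 2.76 | 0.529 | 0.727 | 0.169 | 0.507 | 0.938 |
| 13 | 2.99 | 0.501 | 0.708 | 0.096 | 0.594 | 0.903 |
| exactly 3 months | 3.00 | 0.500 | 0.707 | 0.093 | 0.598 | 0.901 |
| 14 | 3.22 | 0.475 | 0.689 | 0.051 | 0.674 | 0.858 |

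**4. What the unstated interval from enrolment to Day 1 does.** A scan on Cycle 6 Day 1 with an assumed lead of 0, 1, 2 or 4 weeks falls at week 10, 11, 12 or 14 of the table. The lead is an assumption; the protocol gives only a screening window of up to 28 days, with enrolment after screening is complete.

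**5. Recalibrating to week 10.** Keeping 9/16 and 43 patients, with rates 58.8% and 76.7%:
- At least 29/43: alpha 0.153, power 0.933.
- At least 30/43: alpha 0.092, power 0.886.

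No final cut-off at this sample size meets both 10% and 90%.

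**The case against.** The tempting stronger reading is that the primary scan is at week 10 and the true type I error is about 42%. The documents do not support that, for four reasons.

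- Sections 8.1.2 and 9.1 name Cycle 6 without a day. The V6 column favours the visit day, but the end of the cycle (week 12) is not excluded.
- PFS starts at enrolment, not at Day 1, and a lead before Day 1 moves the reading later. With a 4-week lead the error is about 0.05, so even its direction is not fixed.
- Section 6.2.2 allows extended rest periods. Delays push a cycle-anchored scan later. The 0.42 needs every patient to be on time and enrolled on Day 1.
- The schedule counts two visits as a month, so V6 closes M3 and the scans at V6, V12 and V18 look like shorthand for months 3, 6 and 9. If months of 4 weeks are applied to the hypotheses too, the end of Cycle 6 is exactly 3 months and alpha is 0.093. Section 8.3.2, which places Cycle 5 Day 1 at Day 90 although it is 56 days after Day 1 on 2-week cycles, also suggests that calendar months were intended.

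In addition, section 9.3 counts symptomatic progression and death, so not every event between week 10 and month 3 would go unseen.

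All of this stands against treating week 10 as settled. None of it removes the contradiction: an intended 3 months is not what a site reads in sections 8.1.2 and 9.1, and the week-12 calendar reading still gives 0.17. An analysis plan, which was not available here, could define a window but could not move a scan already taken.

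**Conclusion.** The scan timing is internally inconsistent, and the protocol does not fix when the primary endpoint is read. The decision rule is correct for a reading about 3 months from enrolment and loses its stated properties away from it. For a regimen with the null median of 3 months, the chance of a positive result runs from 0.42 (week 10) to 0.05 (week 14), against 0.093 as designed. The chance of stopping at stage 1 runs from 0.32 to 0.67, against 0.60. At week 14 the cost is power, which falls to 0.858.

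These figures rest on the protocol's exponential model, on one common reading time for all patients, and on success meaning not progressed at that time. The upper end is a worst case, not an estimate of the trial's error rate. The point should be settled because following the cycle schedule as written can break the 10% alpha, and the repair is small.

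**What to change.** **Preferred.** In Figure 1a and sections 8.1.2 and 9.1, tie the primary CT to one calendar time counted from enrolment, whatever the cycle number, in line with footnote i. Week 13 ±1 week would serve. Keep the window narrow and centred, because a reading consistently at its early edge (week 12) already gives 0.17. The hypotheses, cut-offs and sample size then stay as they are. The cost is moving one existing scan, with none added. The downside is that it may fall between infusion visits: with enrolment on Day 1, week 13 lies between V7 (week 12) and V8 (week 14).

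**If the Cycle 6 scan is kept.** State which day of Cycle 6 is meant and how enrolment relates to Day 1. Then restate both rates, the final cut-off and the power for that time. For week 10 this is 58.8% versus 76.7% with at least 30/43, giving alpha 0.092 and power 0.886. That power is below the stated 90%, so either the lower figure is accepted openly or the sample size is worked out again. A cycle anchor would also still move with treatment delays.
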